## Methods

### Study design

This study is an open-label, single-arm, mixed-methods feasibility testing of a support and decision-aid clinician-facing platform. Real-world testing will take place within the integrated care board, NHS Greater Manchester (the single site), with four to seven general practitioner (GP) surgeries participating across this large multicultural British city. The study contacted all practices within this area, and five practices responded positively. The study started recruitment for clinical participants on 28/08/2024. Live clinical testing started in March 2025, and the end of the study is 08/09/2025. Each participating practice serves a population of approximately 285 diabetes patients. Therefore, within the study period, it is anticipated that ~665 people with diabetes will attend their primary care practice for a diabetes check.

We will recruit one or two clinician participants from each of 5 GP practices, for a maximum of 10, to ensure the device is used in a variety of diabetes-related clinical settings and comprises a broad range of age groups, ethnicities and medical needs. Clinician participants will be members of the multidisciplinary team (GPs, specialist registered nurses (RNs) and advanced nurse prescribers who regularly see people with diabetes as part of their day-to-day work. They will provide a real-world perspective on how well the system integrates within the normal clinical workflow and provide feedback on how well the system performs. Sample size is calculated to withstand a small number of dropouts, while being large enough to draw out user views with different qualitative and quantitative methods and detect any safety issues across the long term. Each clinician participant will be invited to interview across the testing period (up to a maximum of 10 interviews). This is based on the narrow and focused scope of the interviews, collecting rich interview data by continuous interviewing throughout the study and the variety of HCPs involved in diabetes care in the primary sector and the anticipated number to reach data saturation for this type of study.

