Clinical impact	Routinely collected clinical data System navigation data Weekly questionnaire data	Number of patients with the following care processes recorded within the past 12 months: HbA1c, blood pressure (BP), serum cholesterol, serum creatinine, urinary albumin, foot screening, body mass index and smoking status. Each will be expressed as a percentage of the total number of people with diabetes seen by participants within the study period (and binomial proportion CI). Analysis will be stratified in accordance with diabetes type, age, gender, ethnicity and socioeconomic status (derived via the English index of multiple deprivation score) Number of patients meeting the following treatment targets: HbA1c <58 mmol/mol, BP=<140/80 mm Hg, Cholesterol <5 mmol/L, as well as the number meeting all three targets. Each will be expressed as a percentage of the total number of people with diabetes seen by participants within the study period (and binomial proportion CI) Number of patients with reclassified diabetes diagnosis, expressed as a percentage of the total number of people with diabetes seen by participants within the study period (and binomial proportion CI) and calculated on a monthly basis to demonstrate secular trends (if any) Number of patients with a modification in number of/dose/type of diabetes-related prescriptions (ie, insulin, metformin, DPP-4 inhibitors, pioglitazone, sulphonylurea and/or SLGT2-inhibitors) expressed as a percentage of the total number of people with diabetes seen by participants within the study period, calculated on a monthly basis to demonstrate secular trends (if any). Subjective assessment of system impact—recorded via a 5-point Likert scale. The distribution of scores will be expressed as a percentage of responses received Free-text comments submitted via questionnaire were analysed for emergent themes Number of participant interactions with the system, time spent within the system (cumulative total and per patient)
System appropriateness/applicability	Weekly questionnaires Semi-structured interviews	Clinical usefulness score recorded within weekly questionnaire for each of the MWIQ features (diabetes subtype predictor, diabetes drug response predictor and diabetes complications predictor) as well as overall experience. The score will be recorded via a 5-point Likert scale, and the distribution of scores will be expressed as a percentage of responses received Free-text comments will be analysed for emergent themes

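### The care-process measure under clinical impact looks back 12 months although MWIQ is live for only about 5.3 to 6.3 months, so its single percentage cannot separate care before MWIQ from care during its use

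*Protocol article*

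**What the plan says.** In the protocol article, the section Data collection (Table 2) gives the measures for the secondary outcome "Clinical impact". The first is the "Number of patients with the following care processes recorded within the past 12 months", covering eight processes: HbA1c, blood pressure, cholesterol, creatinine, urinary albumin, foot screening, body mass index and smoking status. Each is "expressed as a percentage of the total number of people with diabetes seen by participants within the study period", with a binomial confidence interval, and is stratified by patient characteristics but not by time. The next measure is the percentage meeting the HbA1c, blood pressure and cholesterol targets, over the same denominator.

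Two other measures in the same row, reclassified diagnosis and changed prescriptions, are calculated month by month to show trends. The care-process and target measures are not.

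Study design describes a single-arm study and gives the dates: "Live clinical testing started in March 2025, and the end of the study is 08/09/2025". Research question asks about MWIQ in comparison with usual care.

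**The concern.** A measure of a system's impact should respond mainly to care given once the system is in use. Here the look-back is about twice the longest possible live period. A urine albumin test from October 2024 would count exactly as one prompted by MWIQ in June 2025, if both fall inside the window. The percentage can therefore look good when MWIQ has done nothing, and a real change is diluted by care that MWIQ could not have influenced.

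Nothing else stated for this measure separates the two periods. There is no control arm, and the article gives the measure no baseline value, no before/after split and no monthly series. The targets are affected in the same way: a single percentage can rest on values measured before MWIQ was used.

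The stakes are moderate. Study aim names clinical impact as one of three areas of clinical performance and says that a successful outcome will support a regulatory submission. A high completion figure under that label could be taken there as evidence of benefit.

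**Working it through.** **Inputs (protocol article)**
- Look-back: 12 months, taken as 365 days (Table 2). No anchor date is stated.
- Live period: a day in March 2025, not given, to 08/09/2025 (Study design).
- Attendance figure: "Each participating practice serves a population of approximately 285 diabetes patients"; "five practices responded positively"; "it is anticipated that ~665 people with diabetes will attend their primary care practice for a diabetes check" (Study design).

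**1. The plan's own attendance figure.** Assume one check per patient per year (not stated). Five practices hold 5 × 285 = 1,425 patients. Then 665 / 1,425 = 46.7% of a year, or 5.6 months (about 170 days). Counting back from 08/09/2025 gives a go-live of about 22 March 2025, which fits the stated March start. The match is not unique: 4 × 285 × 7/12 and 7 × 285 × 4/12 also give 665. The figure is consistent with a live period of about half a year but does not prove it.

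**2. Length of the live period, L.** From 1 March, L = 191 days (6.3 months). From 31 March, L = 161 days (5.3 months).

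**3. Share of the look-back window that precedes go-live.**
- Anchored at study end: 1 − L/365.
- Anchored at each visit, with visits assumed evenly spread over live testing: a visit falls on average L/2 days after go-live, so the mean share is 1 − (L/2)/365.

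| Go-live | L (days) | Anchored at study end | Anchored at visit (mean) |
|---|---|---|---|
| 1 March | 191 | 174/365 = 47.7% | 1 − 95.5/365 = 73.8% |
| 15 March | 177 | 188/365 = 51.5% | 1 − 88.5/365 = 75.8% |
| 31 March | 161 | 204/365 = 55.9% | 1 − 80.5/365 = 77.9% |

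**4. Share of counted patients who qualify only through care before go-live.** This is a different quantity, because a patient counts once if any record falls in the window. Let q be the probability that a patient who is seen has the process recorded after go-live, and b the probability of a record in the earlier part of the window. Take the two as independent. The share is (1 − q)b / [1 − (1 − q)(1 − b)]. For example, q = b = 0.5 gives 0.25/0.75 = 33%. Neither q nor b is in the document, so a range is assumed:

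| q | b = 0.3 | b = 0.7 |
|---|---|---|
| 0.2 | 55% | 74% |
| 0.5 | 23% | 41% |
| 0.8 | 7% | 15% |
| 0.95 | 2% | 4% |

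The result runs from 2% to 74%. The window arithmetic in step 3 does not settle it.

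**5. The denominator.** The article does not define the study period. If it began with clinician recruitment ("The study started recruitment for clinical participants on 28/08/2024"), it would last 376 days (12.4 months), and visits before go-live would enter the denominator too.

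**The case against.** The strongest reply is that the measure was never meant to isolate an effect. The list of strengths and limitations confines the quantitative work to description and calls the data feasibility data. Data collection and Quantitative data collection present the routine data as an overview of the population served. For that purpose a 12-month indicator is coherent: a window cut to five or six months would class a patient tested seven months ago as lacking the process. The measure is one of several under a secondary outcome, the primary outcome is safety, and the article attaches no test or success threshold to this percentage. The choice of extraction date and of which value to use may also sit in the full protocol or analysis plan, which are not shown.

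Much of this stands. It lowers the severity, and the missing anchor date is not a fault in itself. It does not remove the mismatch, because the article itself fixes the 12-month window, the denominator and the impact label, and these do not fit a live period of 5.3 to 6.3 months under any in-study anchor.

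A reader might go further and infer that at least half of what the measure counts, or most of it, is care from before MWIQ. The document does not support that. A share of calendar time is not a share of counted patients (step 4). People seen for a check may well have the process recorded at or near it. Even as calendar time the lower bound is 47.7%, and the 74% to 78% figure needs visit anchoring and evenly spread visits, neither of which the text states.

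**Conclusion.** The concern holds in a limited form. The look-back exceeds the live period, so part of the window always precedes go-live: 48% to 56% if anchored at study end, or about 74% to 78% on average if anchored at evenly spread visits. The ranges reflect the unknown day in March. Followed as written, the plan yields a percentage that mixes care before and during MWIQ use, with nothing stated for this measure that would separate them. The target percentages have the same weakness. The proportion of counted patients who owe their place only to earlier care is unknown and could lie well below or above half. Given the descriptive aim and secondary status, the severity is moderate.

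**What to change.** For the people seen by participants during live testing:

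1. Report the same 12-month care-process percentages, and the target percentages based on the latest value, at go-live (or just before each patient's first MWIQ consultation) and again at study end. State which date is used.
2. Report separately the processes first recorded on or after that date. This is needed because 12-month windows ending at go-live and at study end overlap by 174 to 204 days (365 − 191 to 365 − 161).
3. Describe any difference as an uncontrolled before/after comparison. Attendance for a check raises completion with or without MWIQ, patients who are remeasured are selected, and values that were high at the start tend to fall through regression to the mean.
4. Treat the single 12-month percentage as a description of the population and not as MWIQ impact.

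The cost is a date-stamped extraction of routine data, a second tabulation and revised wording. Fewer patients will have a value after the index date, so those intervals will be wider. Follow-up after a patient-level index date would range from about six months to almost none. The change makes the description interpretable, but it does not supply the comparison with usual care that the research question asks for.

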### Research question

Is the use of MWIQ safe, appropriate, usable and effective when used by primary care HCPs involved in the care of people with diabetes, in comparison to usual care?

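### The care-process measure of clinical impact looks back 12 months over a live period of about 5.3 to 6.3 months and has no stated pre-MWIQ reading, so the single percentage mixes earlier usual care with any MWIQ effect

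*Protocol article*

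**What the plan says.** In the Data collection section, Table 2, the Clinical impact row begins with "Number of patients with the following care processes recorded within the past 12 months". The eight processes are HbA1c, blood pressure, serum cholesterol, serum creatinine, urinary albumin, foot screening, body mass index and smoking status. The denominator rule begins "Each will be expressed as a percentage of the total number of people with diabetes seen by participants within the study period (and binomial proportion" and goes on to name a confidence interval. Results are to be stratified by five factors.

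The Study design section gives the calendar: "Live clinical testing started in March 2025, and the end of the study is 08/09/2025". It also expects that "it is anticipated that ~665 people with diabetes will attend their primary care practice for a diabetes check". The design is single-arm, while the Research question asks about effectiveness "in comparison to usual care".

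The article does not say on which date the 12 months end, and for this measure it states no reading before MWIQ. Two neighbouring measures in the same row, reclassified diagnosis and prescription changes, are to be calculated monthly so that trends can be seen. The care-process measure has no such feature.

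**The concern.** A measure presented as the impact of a tool should count events that the tool could have influenced. A blood test recorded before MWIQ was switched on cannot be its effect, yet it counts as a success if it falls within the 12 months. With a live period of roughly half a year, much of the window belongs to ordinary care.

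The risk is misreading. A high percentage could be taken as evidence of benefit when it mainly shows that the practices already kept good records. A low one could hide a real improvement from a poor start. The article says that the results will support a regulatory submission, so the label on this figure matters even in a descriptive study.

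**Working it through.** **Inputs.** From Study design: go-live in March 2025 (day not given, so 1, 15 and 31 March are tried), study end 08/09/2025, about 665 patients seen. From Table 2: look-back of 12 months, taken as 365 days. The article states no figure for the pre-MWIQ share, so there is nothing to reproduce.

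**Step 1. Length of live use, L.**
- Go-live 1 March: L = 191 days (6.3 months)
- Go-live 15 March: L = 177 days (5.8 months)
- Go-live 31 March: L = 161 days (5.3 months)

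**Step 2. Smallest possible pre-live share.** A window ending no later than the study end holds at most L live days, so the share before go-live is at least 1 − L/365:
- 1 − 191/365 = 47.7%
- 1 − 177/365 = 51.5%
- 1 − 161/365 = 55.9%

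If data were extracted after the study end, the same percentages would be the minimum share of the window lying outside the live period.

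**Step 3. Dependence on the anchor.** Visits are assumed to be spread evenly over the live period. For rows 2 and 3 the mean share is 1 − L/(2 × 365), and the proportion of patients with at least 90% of the window before MWIQ is 36.5/L.

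| Window ends at | MWIQ counted from | Share of window before MWIQ |
|---|---|---|
| Study end | Go-live | 47.7-55.9% for everyone |
| Patient's visit | Go-live | Mean 73.8-77.9%; 19-23% of patients reach 90% |
| Study end | Patient's own visit | Mean 73.8-77.9%; 19-23% of patients reach 90% |
| First MWIQ consultation | That consultation | Essentially 100%, apart from entries made that day |

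**Step 4. What the planned percentage would show.** The article gives no baseline completeness, so 70% and 90% are assumed for one process. Suppose that half of the gaps are closed after first MWIQ use and that no earlier record drops out of the window. Intervals are exact binomial, 95%.

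| Quantity | 90% complete before | 70% complete before |
|---|---|---|
| Recorded before, of 665 | 598 (89.9%) | 465 (69.9%) |
| Gaps | 67 | 200 |
| Closed | 34 | 100 |
| Planned figure | 632/665 = 95.0% (93.1-96.6) | 565/665 = 85.0% (82.0-87.6) |
| Paired change | 34/665 = 5.1 points | 100/665 = 15.0 points |
| Gap closure | 34/67 = 50.7% (38.2-63.2) | 100/200 = 50.0% (42.9-57.1) |

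The same behaviour, half of the gaps closed, appears as 95% or 85% on the planned measure, depending on earlier care. A practice at 95% with no MWIQ effect would also report 95%.

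**Step 5. Side check.** If each patient has one check a year, 5 practices × 285 × 5.6/12 = 665, which fits the live period. The argument does not depend on this.

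**The case against.** **The study is descriptive.** The article limits the quantitative analysis to description, calls the data feasibility data and says that routine data give an overview of the population. Table 2 sets no threshold for this measure, and the same row has other measures of impact. This limits the consequence. It does not remove the mismatch, because the window, the denominator and the impact label are all stated, and a descriptive figure should still describe what its label says.

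**The article is condensed.** The anchor date, the extraction schedule and a reading at go-live may stand in the full protocol or the SAP. Their absence here is not held against the plan. The anchor alone, however, cannot bring the pre-live share below about half. A go-live reading would meet the point, provided that it is used for this measure.

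**Two stronger readings are tempting.** A reader might infer that nearly all of the window precedes MWIQ for most patients. That holds only if the window ends at the patient's own first MWIQ consultation, and the article fixes no such anchor. A reader might also infer that the 12-month measure is insensitive. Step 4 shows that it moves, by 5 or 15 points in the examples, and at 90% the later interval excludes the earlier value. What is missing is the reading that would make the movement visible.

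**Share of window is not share of records.** Records may cluster around the check itself, and clinicians can enter data in the system at the visit. This stands: the 48-56% describes time, not the fraction of records that predate MWIQ.

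**Gap closure has no comparator either.** This also stands. A routine diabetes check closes gaps with or without MWIQ.

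**Conclusion.** The point holds as a mismatch between a stated look-back and a stated live period. At least about half of the window (48-56%) precedes go-live. The share averages about three quarters under the two intermediate anchors with evenly spread visits, and is essentially the whole window under a first-consultation anchor. Because no pre-MWIQ reading is stated, the single percentage combines earlier usual care with any MWIQ effect and cannot by itself indicate impact.

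The shares rest on the article's dates, with the go-live day unknown within March. The three-quarters figure also assumes evenly spread visits. The 95% and 85% examples rest on assumed completeness and are illustrations only. The documents do not support saying that the measure cannot respond to MWIQ, or that it shows no effect. This is a secondary measure in a feasibility study, so the change is worth making but does not threaten the primary safety objective.

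**What to change.** 1. Keep the 12-month percentage as a description of the population, and state the date on which the window ends.
2. For Clinical impact, compute the same 12-month status for the same patients twice: immediately before the first MWIQ-supported consultation (or at go-live), and at data extraction. Report the paired change for each process with its interval.
3. Alongside it, report the number and percentage of processes outstanding at first MWIQ use that were then recorded by data extraction.
4. State that both results are uncontrolled and descriptive, because a routine check also closes gaps.

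**Cost.** The wording of Table 2 and of the analysis plan changes, with modest extra analysis and no new collection from patients. Gap-closure denominators are small: about 67 patients per process if 90% are already complete (an assumption). Intervals would then be about 25 percentage points wide (38.2-63.2%), and the numbers would be too few for stratification by the five factors. The change also assumes that the extract carries record dates. The article does not say so, but a 12-month criterion already requires them. The date of the first MWIQ consultation must be linkable too; using go-live for the first reading of the paired change avoids that need there.

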### MyWay intelligence quotient (MWIQ)

MWIQ V.1.1 is an online electronic platform that provides clinical decision support around the diagnosis and treatment of patients with diabetes and will be delivered as part of the MyWay clinical and MyWay diabetes patient-facing platforms. The MWIQ clinician interface tool contains ~70 predictive models, generated through machine learning techniques and developed by MyWay digital health (MWDH). These models will be operationalised to predict glycaemic/metabolic response to type 2 diabetes pharmacological treatments, diagnosis of rare diabetes subtypes and risk of diabetes-related complications. In addition, they will provide a clinical overview of patient populations.

MWIQ machine learning models were developed through validated literature-based models, then the development of meta-models derived from them and the creation of de-novo models.

The validated literature and meta-models development predict diabetes subtype, diabetes acute and a large range of chronic complications, including cardiovascular disease, renal complications, amputation, blindness, hypoglycaemia, hospitalisation, re-hospitalisation, mortality, etc, and response to lifestyle interventions. The drug response prediction uses multi-dimensional time series data to predict the likely response to defined medications (counterfactual conditions) in domains of interest (HbA1c, blood pressure (BP), etc). Predicted outcomes guide individual therapeutic choice.

MWIQ will provide clear guideline-linked evidence-based decision support, particularly helping primary care staff who may lack specialist knowledge, by building on basic rule-based decision support, which has previously been shown to improve compliance with the guidelines by around 3–4 fold.^17^ Another important feature of the MWIQ system is the human factors approach, which is built into the development and research from the start.^18^

MWIQ aims to improve adherence to existing guidelines, while providing tailored treatment and diagnostic recommendations (within these existing guidelines) to improve future clinical outcomes (figures1  2). MWIQ is not intended to replace the care provided by licensed healthcare professionals (HCPs), involving prescribing, diagnosis or treatment. The system is supportive and advisory. Any treatment decision ultimately requires clinical judgement, taking the full clinical scenario into consideration.

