## Testing protocol

Clinical participants attend an information session and provide written informed consent to the study team before being trained in the use of the system. No additional software is required to access the MWIQ system, and the validators and clinician participants do not require any additional expertise to operate the system. Validators and clinician participants are given an online link before they start testing. Once signed into the system, they can review a patient’s record. Only clinician participants can input any additional clinical data, for example, test results or changes in smoking status, to generate outputs from the system. The system will not generate an output if there is insufficient clinical data input.

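### The prescribing measure under Clinical impact mixes routine and MWIQ-prompted changes and cannot separate them

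*Protocol article*

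**What the plan says.** In the protocol article, Data collection, Table 2, the Clinical impact row counts the "Number of patients with a modification in number of/dose/type of diabetes-related prescriptions" for a listed set of diabetes drugs. It is "expressed as a percentage of the total number of people with diabetes seen by participants within the study period, calculated on a monthly basis" so that any secular trend can be seen. The care-process, treatment-target and reclassified-diagnosis proportions in the same row carry a binomial CI. This one does not.

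The sources named for the row are "Routinely collected clinical data System navigation data Weekly questionnaire data". Use of the system is a separate measure: "Number of participant interactions with the system, time spent within the system (cumulative total and per patient". The definition of the prescribing measure does not refer to it.

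Four other places bear on the reading:

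- MyWay intelligence quotient (MWIQ): "Predicted outcomes guide individual therapeutic choice", but the system is advisory and the treatment decision rests on clinical judgement.
- Testing protocol: "The system will not generate an output if there is insufficient clinical data input".
- Study design: where a validator raises a safety concern, clinicians are advised to stay out of that record until it is resolved.
- Study design and Research question: "This study is an open-label, single-arm, mixed-methods feasibility testing of a support and decision-aid clinician-facing platform", while the question is put for professionals "involved in the care of people with diabetes, in comparison to usual care".

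**The concern.** A diabetes check is an occasion on which prescriptions change with or without decision support. The measure gives the same score to three kinds of patient: one whose change followed the MWIQ advice, one whose change departed from it, and one whose clinician never opened MWIQ. The design has no comparator arm, and the article describes no pre-MWIQ rate for this measure, so nothing in the figure allows routine change to be subtracted.

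The results are meant to support a regulatory submission and to inform later intervention studies. A percentage that appears under the label Clinical impact could be taken there as the effect of MWIQ on prescribing, although it would be the same whether the advice was mostly followed or mostly set aside.

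**Working it through.** **Who is counted.** Setting the sections side by side:

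| Patient seen by a clinician participant | In denominator? | Can enter numerator? |
|---|---|---|
| MWIQ opened, change agrees with advice | yes | yes |
| MWIQ opened, change does not agree with advice | yes | yes |
| MWIQ opened, no output because data are insufficient (Testing protocol) | yes | yes |
| Record not to be accessed because of a safety flag (Study design) | yes | yes |
| MWIQ simply not opened | yes | yes |

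**The denominator.** Study design anticipates about 665 attenders and about 285 diabetes patients per practice. With 5 practices, 5 × 285 = 1,425, and 665 / 1,425 = 46.7% would have to attend. With 7 practices, 7 × 285 × 4/12 = 665. The attending fraction is not stated, so 665 can be neither confirmed nor refuted. It is used here only to set the scale.

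**What the measure can show.** Let *b* be the share of patients whose prescription would change anyway, *u* the share for whom MWIQ is opened, and *a* the share of otherwise unchanged patients, among those opened, whose prescription changes because of MWIQ. The article gives none of these; all values below are assumptions. The reported proportion is

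p = b + (1 − b) × u × a.

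| b | MWIQ never opened (u = 0): patients counted | MWIQ always opened (u = 1), a = 10%: p | Patients counted | Share of those due to MWIQ, (p − b)/p |
|---|---|---|---|---|
| 10% | 67 | 19% | 126 | 47% |
| 20% | 133 | 28% | 186 | 29% |
| 30% | 200 | 37% | 246 | 19% |
| 40% | 266 | 46% | 306 | 13% |

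An observed 28% fits b = 28% with no MWIQ effect. It fits equally well b = 20% with u = 1 and a = 10%, since 0.20 + 0.80 × 0.10 = 0.28, an effect of 8 points.

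**Precision is not the issue.** For p = 28% and n = 665, the 95% half-width is 1.96 × √(0.28 × 0.72 / 665) = 3.4 points. Over the scenarios in the table it runs from 2.3 to 3.8 points, ignoring clustering.

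**What a split by use adds.** Take b = 20%, a = 10% and half of the patients opened, with opening unrelated to the background rate. Overall p = 0.20 + 0.80 × 0.5 × 0.10 = 24%. Split, it is 28% among the 332.5 opened and 20% among the 332.5 not opened, with half-widths 1.96 × √(0.28 × 0.72 / 332.5) = 4.8 and 1.96 × √(0.20 × 0.80 / 332.5) = 4.3 points. With b = 24% and no effect, the overall figure is again 24%, but under the same assumption both groups show 24%. The split therefore carries information that the planned figure loses. It is not proof of effect: 28% against 20% would also arise with no effect if clinicians opened MWIQ mainly for patients whose treatment they were already minded to change.

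**The case against.** The strongest reply is that the article claims no attribution. Its strengths and limitations confine the quantitative work to description, the study is called feasibility testing, and routine data are said to give an overview of the population. The measure also sits beside a rating of system impact, free text, interviews and usage data, and the Analysis section promises triangulation. This stands as a reason to keep the severity moderate. It does not remove the point, because a descriptive figure should still describe what its label says. Triangulation of summaries does not link a prescription change to use of MWIQ in the same patient, and a monthly trend within the study period cannot tell MWIQ from other causes.

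It could also be said that linkage belongs in the fuller protocol or the SAP. The article, however, fixes this measure completely, with numerator, denominator, drug list and time unit, and the definition contains no condition on use.

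Two stronger readings are tempting and are not supported. A reader might infer that the measure captures routine prescribing only and no MWIQ impact. It does not exclude impact: any MWIQ-prompted change is counted, but cannot be identified. A reader might also infer that counting changes in any direction is a fault. The Introduction names unsuitable medication, unnecessary insulin and polypharmacy as problems, so starting, stopping, reducing or switching could each reflect use of the system, and the article states no preferred direction.

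Finally, agreement with advice is not influence. MWIQ recommends within existing guidelines, so a clinician may make the agreeing change unprompted. This stands, and it limits what the fix may claim.

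**Conclusion.** The concern holds in this form: the prescribing measure combines routine and MWIQ-prompted change over all patients seen, whether or not MWIQ was opened, gave an output or could be accessed, and cannot separate them. On its own it should not be presented as impact of MWIQ.

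The conclusion rests on the definition in Table 2 and not on any assumed rate. The sizes are illustrative: with 665 patients and background rates of 10% to 40%, about 67 to 266 would be counted with no use of MWIQ at all. The missing CI is a small inconsistency with the neighbouring proportions and has no bearing on attribution.

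This is a secondary outcome in a descriptive study, so the change is worth making but does not threaten the primary safety objective.

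**What to change.** 1. Report the measure separately for patients whose record was opened in MWIQ and those whose record was not, each with a binomial CI as for the neighbouring proportions. Opened should mean opened by the clinician participant around the consultation, since validators also review these records.
2. Where displayed recommendations are stored, also report among opened records the proportions with a change that agrees with the recommendation, another change, and no change.
3. Keep the overall figure, labelled as descriptive prescribing activity.
4. State beside the table that the split describes use and agreement, not causation, because opening may be selective and there is no comparator.

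The cost is some linkage and programming, with no new data from clinicians. Item 1 assumes that the navigation log identifies the patient and the user. The article mentions interactions and time, including time per patient, but not the log's structure. Item 2 assumes that recommendations are stored with the system version in force, because MWIQ is improved during testing; the article does not say so. If they are not stored, items 1, 3 and 4 can still be done.
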